### Plans to give access to the full protocol, participant-level data, and statistical code {31c}

The participant-level dataset and statistical code generated during the current study will be available from the corresponding author on reasonable request after the trial is finished.

## Oversight and monitoring

### Composition of the coordinating center and trial steering committee {5d}

Two committees have been established to manage the trial, including a trial steering committee and a data monitoring committee. The steering committee composes of cardiologists from the First People’s Hospital of Yibin and investigators from Zhejiang University. The major responsibility of the steering committee is to evaluate and study protocol, communicate with the ethics committee, and supervise the practice of hypertension management for both 2 groups.

### Composition of the data monitoring committee, its role and reporting structure {21a}

The data monitoring committee consists of statisticians from Zhejiang University. This committee is independent from the sponsor and has no competing interests. The committee will be in charge of auditing the trial every quarter to oversee the data quality of the study. The committee charter is available from the corresponding author.

### Adverse event reporting and harms {22}

Serious adverse events will be collected and recorded for further analysis at the end of the trial. These events include deaths, emergency room visits, and hospitalization longer than 24 h. Investigators will explore the correlation between these events and patients’ healthcare records.

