**Fig. 2 Fig2:**
[figure not shown]
System architecture

In this trial, all the interventions will be conducted through the system. The intervention group will gain full access to the system and manage their hypertension under the guidance of the model. The control group will only gain partial access to the system (only for BP measurement) and receive care as usual. Table 1 summarizes all the interventions for each group.

**Table 1 Tab1:** All the interventions for the 2 groups

Intervention category	Execution method in the control group	Execution method in the intervention group
Diagnosis	By physicians (before the trial)	By physicians (before the trial)
Risk assessment	No execution	Conducted by GPs with the assistance of the system; reassessed based on self-monitoring data per week
Hierarchical management	Executed by the system based on patients’ BP values; only adjusted after regular follow-up; no management plans for patients	Executed by the system based on patients’ risk level per week; provide executable management plans to patients
Regular follow-up	Performed by GPs once every 3 months for level 1 patients and once every 2–4 weeks for level 2 patients; no dynamic adjustment	Performed by GPs once every 3 months for level 1 patients and once every 2 weeks for level 2 patients; dynamically adjusted based on patients’ management level
Abnormal condition intervention	No execution	Conducted by GPs; abnormal condition is informed by the system
Compliance management	No execution	Conducted by CMs; compliance is calculated by the system per week
Medication guidance	Provided by GPs during regular follow-up	Provided by physicians or GPs through the system anytime
Lifestyle guidance	Provided by GPs during regular follow-up	Provided by physicians or GPs through the system anytime
Health education	Provided by GPs during regular follow-up	Conducted by CMs through the system, mainly in the form of online materials

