### Outcomes {12}

The primary outcome of the trial is changes in mean systolic blood pressure (SBP) from baseline (T0) to 12 months (T2). The key secondary outcomes are changes in mean diastolic blood pressure (DBP) and changes in biochemical indexes related to hypertension from T0 to T2. The other secondary outcomes include changes in lifestyles, self-management adherence, and hypertension awareness from T0 to T1 (6 months) and T2. In addition, work efficiency of care providers will be assessed at T2 to validate the model from a care provider perspective.

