## Data collection and management

### Plans for assessment and collection of outcomes {18a}

Data collection will be mainly conducted at T0, T1, and T2. Table 2 shows the complete outcome measures and their collecting methods. The details are described in the following sections.

**Table 2 Tab2:** The complete outcome measures and their collecting methods

Outcome measure		Collecting method
Systolic blood pressure		Clinic BP measurement
Diastolic blood pressure		Clinic BP measurement
Biochemical indexes	Blood urea nitrogen (BUN)	Laboratory test (blood test)
	Creatinine (Cr)	Laboratory test (blood test)
	Alanine transaminase (ALT)	Laboratory test (blood test)
	Aspartate transaminase (AST)	Laboratory test (blood test)
	Uric acid (UA)	Laboratory test (blood test)
	Low-density lipoprotein (LDL)	Laboratory test (blood test)
	High-density lipoprotein (HDL)	Laboratory test (blood test)
	Blood glucose (BG)	Laboratory test (blood test)
	Total cholesterol (TC)	Laboratory test (blood test)
	Triglyceride (TG)	Laboratory test (blood test)
Lifestyles	Obesity (BMI and WHR)	Basic body measurement
	Physical activity	Questionnaire (IPAQ)
	Diet (24-h urine sodium and potassium)	Laboratory test (24-h urine test)
Self-management adherence	Medication adherence	Questionnaire (HB-MAS)
	Self-monitoring adherence	System log
Hypertension awareness		Questionnaire (HK-LS)
Work efficiency of care providers	Frequency of follow-up in a day	System log
	Handling time for a follow-up request	System log

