#### Blood pressure

Blood pressure (BP) measurement can be categorized into 2 types: clinic and out-of-office BP measurement [16]. Clinic BP measurement is performed by GPs or CMs under standard conditions and unified guidelines. Out-of-office BP measurement includes ambulatory BP monitoring and home BP monitoring, which can provide large amount of BP data outside the medical environment [30, 31]. In this trial, we will use clinic BP measurement to assess the variation in SBP and DBP from baseline to 12 months and use out-of-office BP measurement (home BP monitoring) to promote interventions in daily management. When performing clinic BP measurement, patients should be seated for at least 5 min in a quiet room before measurements and keep the upper arm at the heart level. Measurements will be conducted at least 2 times and taken 1–2 min apart. An additional measurement will be required in case that the first two readings differ by > 5 mmHg. The mean value of these readings will be recorded.

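### The harms plan names only serious events and no comparison by arm, so low blood pressure short of a serious event would not be reported as harm

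*Protocol article*

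**What the plan says.** Section {22} of the protocol article is its only text on harms. It states: "Serious adverse events will be collected and recorded for further analysis at the end of the trial". It continues: "These events include deaths, emergency room visits, and hospitalization longer than 24 h". The one analysis it names is this: "Investigators will explore the correlation between these events and patients’ healthcare records". No comparison between randomized groups is written there. Low blood pressure, dizziness, fainting and falls appear nowhere in the article.

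Section {18a} says: "Table 2 shows the complete outcome measures and their collecting methods". Table 2 lists blood pressure, laboratory values, lifestyle, adherence, awareness and provider efficiency, but no harm. Under Blood pressure the article says that "we will use clinic BP measurement to assess the variation in SBP and DBP from baseline to 12 months", and Outcomes {12} uses SBP and DBP as changes in means.

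Table 1 gives medication guidance in the intervention arm as "Provided by physicians or GPs through the system anytime". In the control arm GPs give it during regular follow-up. Abnormal condition intervention is conducted by GPs in the intervention arm and is not executed in the control arm.

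**The concern.** The intervention is meant to lower blood pressure through closer, reading-driven management in people aged up to 80. A harm that follows directly from that aim is pressure that falls too low. Where such an episode leads to death, an emergency visit or a long admission, it is recorded, although nothing requires it to be identified as low pressure. Where it does not, no instrument in the article records it as harm.

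The efficacy outcome does not fill the gap. In a change in mean SBP, a patient whose pressure drops too far counts in the same direction as one who reaches target. The trial could report superiority on mean SBP and still be unable to say whether low readings or related symptoms were more common in one arm.

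No other body is given the task. The data monitoring committee audits data quality each quarter, the steering committee supervises management practice, and no interim analysis is planned.

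**Working it through.** **1. The plan's own sample size (section {14}).** Inputs: difference 5 mmHg, SD 16.5 mmHg, two-sided α 5%, power 0.80, 1:1 allocation.

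n per group = 2 × (1.96 + 0.8416)² × 16.5² / 5² = 170.95, so 171 per group and 342 in total, as stated. With 15% attrition, 342 / 0.85 = 402.4 against the stated 402, a rounding difference. The point below does not depend on these figures and does not change them.

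**2. What each instrument would record.**

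| Event | Section {22} | Table 2 and Outcomes {12} |
|---|---|---|
| Low pressure leading to death, emergency visit or stay over 24 h | Recorded, not necessarily labelled as low pressure | Not identified |
| Low pressure or symptoms without such an event | Not named | Clinic value enters the mean change only; symptoms not asked about |
| Comparison of harm by arm | Not stated | No harm measure |

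**3. How much a mean comparison could leave unseen.** The documents give no low-pressure rate and no expected follow-up mean. Assumptions: SBP at T2 is normal; its SD is 16.5 mmHg (borrowed from the sample size section); the intervention mean is 5 mmHg lower; the control mean is 135, 140 or 145 mmHg. The 110 mmHg cut-off is for illustration only and is not proposed as a clinical rule.

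Share below the cut-off = Φ((110 − mean) / 16.5). For a control mean of 140: Φ(−30/16.5) = 3.45% in controls and Φ(−25/16.5)... with the intervention mean of 135 = 6.49%.

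CI half-width = 1.96 × √[(p₀(1−p₀) + p₁(1−p₁)) / 171]. For that case: 1.96 × √[(0.0333 + 0.0607) / 171] = 4.6 points.

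| Control mean | Control | Intervention | Ratio | Expected patients per 171 | Difference ± 95% half-width (points) | Power |
|---|---|---|---|---|---|---|
| 135 | 6.5% | 11.3% | 1.74 | 11.1 v 19.3 | 4.8 ± 6.0 | 34% |
| 140 | 3.5% | 6.5% | 1.88 | 5.9 v 11.1 | 3.0 ± 4.6 | 25% |
| 145 | 1.7% | 3.5% | 2.04 | 2.9 v 5.9 | 1.8 ± 3.4 | 18% |

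With an illustrative 100 mmHg the shares are 0.3–1.7% against 0.8–3.5%, and power is 8–18%.

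**4. A larger assumed excess.** Take 3% in controls and 8% in the intervention arm for low pressure or symptoms (assumed). SE = √[(0.03 × 0.97 + 0.08 × 0.92) / 171] = 0.0245, and 1.96 × SE = 4.8 points. The 5-point difference then has an interval of about 0.2 to 9.8 points, with power of about 53%.

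**The case against.** A reader might infer that harm can only ever be one of the three named events and that the arms will never be compared. The text does not go that far. The named events are introduced as included, not as an exhaustive list. The analysis at the end of the trial is left open, and section {20a} plans summaries and group comparisons of collected data in general terms. What stands is that collection is confined to serious events and that no comparison of harm by arm is stated.

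A reader might also infer that the intervention arm is treated to a lower pressure. The article gives it no lower target and no drug-escalation rule. Its pathway is drawn mainly from the same guidelines. Controls above target are also followed every 2–4 weeks to adjust therapy. The abnormal-reading alert is not limited to high values, so it might even protect against low pressure. The direction of any difference is therefore unknown, which is a reason to report it rather than to presume harm.

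Nor do the documents show that over-lowering would account for much of the apparent benefit. If an extra 5% of patients were 10–20 mmHg lower than otherwise (assumed), the arm mean would move by 0.05 × 10 = 0.5 to 0.05 × 20 = 1.0 mmHg, a minor part of the planned 5 mmHg.

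An article may leave non-serious event definitions to a full protocol or analysis plan. That carries some weight. However, section {22} states which class of event is collected, section {18a} calls its outcome table complete, and Trial status says the manuscript details the original protocol. A low-pressure proportion could be derived later from stored clinic readings. Symptoms never asked about cannot be recovered by any analysis plan.

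**Conclusion.** The concern holds in limited form. As written, the plan collects serious adverse events, names only a correlation with healthcare records as their analysis, and uses blood pressure for efficacy alone. Low pressure short of a serious event would not be reported as harm, in a trial whose arms differ in exactly the management that could affect it.

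Its size cannot be taken from the documents. Under the normal model above, the planned shift alone would multiply the share below 110 mmHg by about 1.7 to 2.0, or roughly 3 to 11 control patients against 6 to 19 intervention patients per 171. Every rate used is an assumption, and power stays well below 80% in all these cases. The gain would be a reported difference with its uncertainty, not a test able to settle the question. The primary analysis and the sample size are unaffected.

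**What to change.** Pre-specify a descriptive safety comparison by arm, reported as differences with 95% confidence intervals and labelled as not powered, covering:

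- the serious adverse events already collected;
- the proportion with clinic blood pressure below a limit that the sponsor's clinicians set in advance, at T1 and T2;
- a short question on dizziness, fainting and falls, worded identically for both arms, at T1 and T2.

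Use home readings only as support, and per reading taken. Controls have no management plans and no compliance follow-up, so measuring frequency may differ by arm and raw counts would mislead.

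The cost is small. The article states that "Data collection will be mainly conducted at T0, T1, and T2", and awareness and adherence are already assessed at T1 and T2, so this adds one derived variable and a few items. Whether clinic pressure is taken at T1 should be confirmed against the schedule figure, which is not reproduced in the text at hand; Trial design {8} refers to repeated measurements at all three times.

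The downsides should be stated with the results: slightly longer questionnaires, imprecise estimates, possible reporting bias in the symptom items because the trial is open-label, and seated clinic readings that miss episodes between visits.

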### Frequency and plans for auditing trial conduct {23}

The trial conduct will be audited by the data monitoring committee once every quarter.

### Plans for communicating important protocol amendments to relevant parties (e.g., trial participants, ethical committees) {25}

All changes to the study protocol will be reviewed by the steering committee, then reported to the sponsor, participating care providers, and investigators.

## Dissemination plans {31a}

The study results will be disseminated via articles published in peer-reviewed journals.

## Discussion

This protocol has been designed to understand the effectiveness of a pathway-driveneHealth-based integrated care model, implemented as a full-featured telehealth system. Compared with prior studies [38, 39], our study innovatively introduces the concept of pathway, then combines it with information technology and the “three-manager” mode to establish a standardized and executable care model. Besides testing efficacy of the model, this study will have several other strengths if successful. First, the model can be generalized to other common chronic diseases, such as diabetes, stroke, and chronic obstructive pulmonary disease (COPD). The task-based pathway can be applied in both single disease and multiple chronic conditions. Second, the study would provide the feasibility evidence of the “three-manager” mode combined with information technology in China. Policy makers in other regions across the country could roll out similar services for better management. Last, the awareness, treatment, and control rates of hypertension in Sichuan, Yunnan, and Guizhou are relatively low compared with other provinces [40]. Therefore, performing such a trial in Yibin is significant to improve the local outcome for hypertension management.

The present protocol is also subject to some limitations. First, since the clients for patients are different from traditional mobile applications, participants may show different levels of acceptance in the system. Low system acceptance will lead to undesirable high attrition rates. We will adopt several strategies to improve patients’ acceptance of the system, including ongoing system updates with usability tests, online system guidance from CMs, and regular offline training sessions for patients. Second, this is an open-label trial for both patients and care providers. Patients in the control group may not comply with self-management regimes or even choose to discontinue the participation, and care providers may tend to conduct the management for the control group not following the guidelines. We plan to eliminate these potential biases through intensive training of care providers and reward mechanism on patients (for example, free outpatient registration), as well as supervision of intervention quality from the steering committee.

### Trial status

This study protocol was approved on 7 November 2019, and this manuscript details the protocol on the original version. Due to the COVID-19 pandemic, the participant recruitment has been adjusted to July 2020. The first participant was enrolled on July 3, 2020, and recruitment is expected to be completed by November 2020.

## Abbreviations

BP: Blood pressure
CMs: Case managers
GPs: General practitioners
HB-MAS: The Hill-Bone Medication Adherence Scale
HK-LS: The Hypertension Knowledge-Level Scale
IPAQ: The International Physical Activity Questionnaire
PEICM: Pathway-driven eHealth-based integrated care model
